## Abstract

**Background:**

A discussion is ongoing whether displaced femoral neck fractures in elderly patients should be treated with a non-cemented or a cemented hemiarthroplasty. A recent Cochrane analysis stresses the importance of further research into the relative merits of these techniques. We hypothesise that non-cemented hemiarthroplasty will result in at least the same technical-functional outcome and complication rate, with a shorter operation time.

**Methods and design:**

A randomised controlled multicentre trial will be performed.

The study population consists of 200 patients of 70 years and older. Patients with a displaced femoral neck fracture will be allocated randomly to have a cemented or a non-cemented hemiarthroplasty. Data will be collected preoperatively, immediately postoperatively, and 6 weeks, 3 months and 1 year postoperatively.

The main outcome measures of this study are technical-functional results of the hemiarthroplasty, duration of surgery, complications, and mid-thigh pain. Secondary outcome measures are living conditions at final follow up, self-reported health-related quality of life, and radiological evaluation of the hemiarthroplasty.

**Conclusion:**

A recent Cochrane analysis did not find arguments in favour of either non-cemented or cemented hemiarthroplasty. The forthcoming trial will compare treatment for a displaced femoral neck fracture by cemented versus non-cemented hemiarthroplasty. Our results will be published as soon as they become available.

**Trial Registration:**

Trial Registration Number NTR1508

## Background

Patients with a hip fracture form a heterogeneous group with a high mortality rate, frequently troubled with multiple and severe co-morbidities. They are usually frail and elderly, with more than 30% aged ≥ 85 years. In European series, hip fracture patients have a 30-day mortality of >10%, and a 1-year mortality of 25–30%.[1] Despite the advances in surgical and anaesthetic techniques during the last 20 years there has been no decrease in mortality after surgical repair of hip fractures. [1]

The discussion about cemented or non-cemented hemiarthroplasty is similar to the discussion about cemented or cementless prostheses in primary hip arthroplasty. With respect to the latter, conflicting data are presented by the Swedish and Norwegian arthroplasty registers. [2,3] The general opinion is that cementless hip arthroplasties are more suitable for younger patients owing to the quality of their bone stock. In hemiarthroplasty for hip fracture surgery there are insufficient data from randomised trials to conclude on the superiority of either type of arthroplasty. Some authors found patients with cemented stems to have less pain and better mobility postoperatively than those with an non-cemented press fit.[4] Mid-thigh pain is frequently reported in primary cementless total hip arthroplasties. However, the reported incidence varies tremendously; D'Lima et al.[5] in a control-matched study reported 34%~vs.~3%, while Grübl et al.[6] in a non-controlled series reported only 3% for cementless primary total hip arthroplasties.

In cemented hemiarthroplasties polymethylmethacrylate bone cement is applied at the time of surgery, forming a solid bond between the prosthesis and the femoral bone; on the contrary, in cementless prosthesis the bonding between prosthesis and femur is dependent upon bony in-growth. Potential advantages of cementing are a less post-operative mid thigh pain, as the prosthesis is firmly fixed within the femur, and a reduced long-term revision rate from loosening of the prosthesis. Major side effects of cement are cardiac arrhythmias and cardio-respiratory collapse, which occasionally occur on application. These potentially fatal complications are caused either by embolism from marrow contents forced into the circulation or by a direct toxic effect of the cement. [7] Another major disadvantage of a cemented prosthesis is that revision arthroplasty will be more difficult.

The non-cemented hemiarthroplasty used in our study is the DB-10 (Biomet, Warsaw, USA), a straight collared stem designed to provide primary stability and to prevent migration. The primary stability of the stem, which has a narrow tip to guide the implant, is optimised by metaphyseal anchoring: intimate trabecular bone contact and optimised load transfer to the dynamic bone through to the posterolateral angle situated in the axis of the neck. Secondary stability (prevention of migration) is facilitated by optimizing bone in-growth surface through full hydroxyapatite coating on macro-structured titanium and grooves on A/P sides.

The cemented hemiarthroplasty used in our study is the Müller Straight Stem prosthesis (Zimmer, Warsaw, USA), developed with the advice of Professor M.E. Müller. It has now been in use reliably for many years; Ried et al. found a 15-year survival of 94%. [8] The fluted structure of the stem, with the two particularly marked longitudinal grooves AP in the stem axis, enables good cement adhesion. The small proximal collar serves to compress the cement, prevents the stem from sinking into the cement, and, together with the fine-blasted surface of the straight stem, achieves a stable anchorage of the implant.

Both prostheses have a unipolar head.

## Methods and design

### Study design

A single blinded randomised clinical multicentre trial will be conducted. Patients will be randomised to 2 groups of 100 in the operation theatre by a randomisation computer (IRIS^®^, SDS Medical, The Netherlands). The treatment will be either a cemented hemiarthroplasty or a non-cemented hemiarthroplasty. If complications occur during the procedure, the surgeon can change the procedure to ensure best medical practice.

We acknowledge the possibility that the patients might be able to tell which prosthesis they have received due to seeing their X ray during the outpatient clinic visits.

All patients with a displaced femoral neck fracture who are admitted to one of the participating hospitals and meet the inclusion criteria are asked to join the study. In case of (mental) incompetence of the patient his/her legal representative is consulted to obtain informed consent.

The study design, procedures and informed consent are approved by the Medical Ethical Committee of South West Netherlands.

Trial number Netherlands Trial Registry NTR 1508, 

### Study population

The study will be conducted at the Orthopaedic Departments of the Reinier de Graaf Gasthuis Delft, Ziekenhuis Rijnstate Alysis Zorggroep Arnhem, Canisius Wilhelmina Ziekenhuis Nijmegen and Elisabeth Ziekenhuis Tilburg.

Authors PP and AV will be responsible for the data and safety monitoring.

Inclusion criteria: patients aged = 70 years, with a displaced femoral neck fracture (Garden type III or IV) not older than 7~days are included.

Exclusion criteria: patients with a pathological fracture, a fracture older than 7 days or ASA-V classification are excluded.

Accrual is planned in the period from August 2008 to August 2009.

### Intervention

Patients will be receive either a cemented hemiarthroplasty, type Müller Straight Stem (Zimmer, Warsaw USA), or a non-cemented hemiarthroplasty, type DB-10 (Biomet, Warsaw USA). Every surgeon will use the same surgical approach for all implants – either straight lateral or posterolateral. The approach of choice is up to the surgeon's preference, as Parker's Cochrane analysis has shown that insufficient evidence is available for superiority of either approach. [9]

Anaesthesia, analgesia and postoperative physical therapy will be standardized in both groups.

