### Determination of sample size

#### (a) Duration of surgery

It is expected that a cemented hemiarthroplasty on average will take 12 min longer than a non-cemented hemiarthroplasty. Taking into account an estimated standard deviation of 12 min, a 1-year mortality of 25% and 10% of patients being lost to follow up or providing insufficient data we need a minimum of 46 patients per group.

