#### (b) Functional outcome

Only for patients who are admitted from their own homes or assisted living facilities, functional outcome is measured by the Timed-Up-and-Go (TUG) score and the Groningen Activity Restriction Scale, and mid-thigh pain a non-inferiority design is used. [10,14]

• TUG performed; Giving the fact that at discharge with a cut-off point of over 30 seconds is significantly associated with falls. Less than 24 seconds is considered good functioning and has hardly any chance to fall. 42 seconds is considered poor functioning with a considerable chance to fall. [14] About 30% of the patients have a poor score at discharge. About 70% of all patients are admitted from their own homes or assisted living facilities. If non-inferiority is considered for TUG, a worsening of score from 30 to 42 is considered clinically relevant, with a SD of 10 sec., giving 16 patients a group. Corrected for the percentage admitted from home or assisted living facility (70%) and the drop out of 35% gives 34 patients a group

• GARS: The GARS data for this group of patients are insufficient to make valid calculations of statistical power. While data for multiple sclerosis patients and healthy older patients are available, there are none for patients with a hip fracture. An estimate is made based on preliminary data from a prospective survey in progress. As soon as sufficient data from this survey are available a final power calculation for GARS will be done.

• Mid thigh pain

Rather varying figures about mid-tight pain are reported in literature. D'Lima [5] reported 40 vs. 3% whereas v/d Wal et al. [15] reported 20 vs. 12% in non-tight proximal fit prosthesis. Therefore the average values of these two studies are taken.

π1 = 30%, π 2 = 7.5%, π = (30%+7.5%)/2 = 18.75%

n_1 _= n_2 _≥ 21* (0,1875*(1-0,1875))/(0,225)^2 ^= 63.2.

If the 25% 1-year mortality combined with expected 10% lost-to follow-up (or missing values) is taken into account this number is raised by 35%, then a total of 86 patients a group is needed. [16]

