### Statistical analysis

#### Primary outcome measures

The differences in operation time, mid-thigh pain, complications and TUG test will be analyzed using a Student's t-test, setting the level of significance at *p *< 0.05.

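### The unadjusted t-test for duration of surgery leaves any surgeon and hospital variation in the error term; a model with hospital, approach and surgeon would cost little and could tighten the estimate

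*Protocol article*

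**What the plan says.** Four statements in the protocol article bear on this point.

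- **Intervention.** Two approaches are allowed, the straight lateral and the posterolateral, and which one is used is a personal choice: "The approach of choice is up to the surgeon's preference". The reason given is that a Cochrane analysis found insufficient evidence that either approach is superior. The choice may not vary with the implant: "Every surgeon will use the same surgical approach for all implants".
- **Study population.** The trial runs in the orthopaedic departments of four hospitals: "Reinier de Graaf Gasthuis Delft, Ziekenhuis Rijnstate Alysis Zorggroep Arnhem, Canisius Wilhelmina Ziekenhuis Nijmegen and Elisabeth Ziekenhuis Tilburg".
- **Study design.** "Patients will be randomised to 2 groups of 100 in the operation theatre by a randomisation computer". Nothing is said about whether the computer balances by hospital, surgeon or approach.
- **Statistical analysis, Primary outcome measures.** "The differences in operation time, mid-thigh pain, complications and TUG test will be analyzed using a Student's t-test", at p < 0.05. No covariate is named.

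The only regression is a logistic one. It stands under Secondary outcome measures, is used only after a significant association, and names no covariates.

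**The concern.** Duration of surgery is a primary outcome, defined as skin-to-skin minutes. Operating time can plausibly differ between surgeons and between hospitals, and approach is fixed within surgeon. Because each surgeon uses one approach for both implants, each surgeon forms a natural block in which the two implants are compared under the same approach. A pooled t-test does not use that block, so whatever variation exists between surgeons and hospitals stays in the residual variance.

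At stake is the width of the interval around the difference in minutes, and the power to detect a difference smaller than planned. The validity of the comparison is not at stake. Covariate detail is often left to an analysis plan that is not shown, but here the article itself names the primary test, so the point concerns a stated method and not an omission.

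**Working it through.** **Inputs from the article.** Expected difference 12 min ("cemented hemiarthroplasty on average will take 12 min longer than a non-cemented hemiarthroplasty"), SD 12 min, 46 per group needed for duration, 100 per group planned, significance level 0.05 (two-sided assumed). Power is not stated. The factor 21 in the mid-thigh pain formula ("≥ 21* (0,1875*(1-0,1875))/(0,225") equals 2 × (1.96 + 1.2816)² = 21.0, which implies 90% power at two-sided 5%.

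**Assumed inputs.** The article gives no variance between surgeons, hospitals or approaches. The share of variance explained (R²), the surgeon intraclass correlation (ICC), the 20 surgeons and the 5 min difference used below are all assumptions.

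**Step 1: the article's own figure.** At 90% power, two-sided 5%, a 12 min difference with SD 12 needs 22 per group. Dividing by 1 − 0.35 for the stated losses gives 34, not 46. The value 21/(0.65 × 0.70) = 46.15 matches, which suggests that the 70% home-admission correction was also applied, although the duration section does not list it. That is a separate matter and does not affect this point.

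**Step 2: is the planned effect at risk without adjustment?** (normal approximation)

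- 46 per group: SE = 12 × √(2/46) = 2.50 min; 12/2.50 = 4.80; power = Φ(4.80 − 1.96) = 99.8%.
- 100 per group: SE = 12 × √(2/100) = 1.70 min; 12/1.70 = 7.07; power over 99.99%.

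It is not at risk.

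**Step 3: the most that adjustment could gain.** At 100 per group the adjusted SE is at best 12 × √(1 − R²) × √(2/100), a reduction of 1 − √(1 − R²).

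| R² (assumed) | SE, min | Reduction | Power for 5 min (assumed) |
|---|---|---|---|
| 0 | 1.70 | 0% | 83.8% |
| 0.10 | 1.61 | 5.1% | 87.4% |
| 0.20 | 1.52 | 10.6% | 90.9% |
| 0.30 | 1.42 | 16.3% | 94.1% |

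These are ceilings. They ignore the cost of estimating the extra terms and any uneven split of implants within a surgeon.

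**Step 4: what adjustment costs if surgeons do not differ.** Simulation of 200 patients randomised 1:1, 20 surgeons, SD 12, true difference 5 min, 4,000 runs per cell. The two models were simulated separately, so the t-test power differs slightly between runs.

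| Surgeon ICC | t-test vs surgeon as fixed effects | t-test vs hospital + approach + random surgeon |
|---|---|---|
| 0 | 83% vs 79% | 83.2% vs 82.7% |
| 0.1 | 85% vs 84% | 83.6% vs 84.6% |
| 0.2 | 84% vs 88% | 83.3% vs 88.1% |
| 0.3 | 84% vs 92% | 83.9% vs 91.5% |

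In a further simulation of the random-effect model, the SE at ICC 0 was 1.71 min against 1.69 for the t-test: 1.71/1.69 = 1.012, a loss of about 1%. Type I error of the random-effect model was 4.3-5.3%. Hospital and approach terms alone gained only 0 to 1.5 points of power, so most of the gain comes from the surgeon term.

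**Step 5: is the t-test itself sound?** With surgeon ICC from 0 to 0.3, its type I error was 4.6-5.7% and its mean estimate 11.9-12.0 for a true 12. It is valid and unbiased.

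**The case against.** The strongest reply is that nothing here is an error. Patients are randomised individually and each surgeon uses one approach for both implants, so approach is not tied to arm. The planned difference is detected almost with certainty either way. The gain rests on a variance that the article does not report, and adjusting for 20 surgeons as fixed effects lost about four points of power when surgeons did not differ. All of this stands, except that the last item argues against fixed surgeon effects only: with a random surgeon effect the loss is about half a point.

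It also stands that the gain is shown for duration alone. The formula 1 − √(1 − R²) belongs to linear models of continuous outcomes. It does not carry over to logistic models for complications or mid-thigh pain, and no gain was calculated for TUG.

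The article also supports neither of two stronger readings that a reader might infer.

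- *Chance imbalance in surgeon or approach biases the implant comparison.* With an assumed 50/50 split of approach, the arms can differ by 1.96 × √(2 × 0.25/100) = 13.9 percentage points by chance. If the approaches differed by 5 min (assumption), that would move the estimate by 0.139 × 5 = 0.7 min, against an SE of 1.70 min. The t-test's standard error and type I error already allow for such movement, as step 5 of the working shows.
- *Randomisation is not stratified by hospital.* The article is silent, but it is a condensed account, and the randomisation computer may stratify without this being reported. Silence is not evidence either way.

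The Cochrane remark in the Intervention section settles nothing here: insufficient evidence of superiority does not show that operating time is unrelated to approach or surgeon.

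**Conclusion.** The point holds as a minor efficiency improvement to the stated analysis of duration of surgery. The unadjusted t-test gives a valid, unbiased answer with ample power for 12 min, but it leaves any surgeon and hospital variation in the error term, although the protocol's own rule of one approach per surgeon makes a within-surgeon comparison available.

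If hospital, approach and surgeon explain 10-30% of the variance, the standard error falls by at most about 5-16%, from 1.70 min to between 1.61 and 1.42 min at 100 per group. If they explain none, it rises by about 1%. The benefit would be a narrower interval and better power for differences well below 12 min. The size depends on the assumed variance share and, in the simulations, on 20 surgeons and a 5 min difference; none of these is in the article.

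**What to change.** Replace the t-test for duration of surgery with a linear model containing treatment, hospital and surgical approach, with surgeon as a random effect, and report the treatment difference in minutes with its confidence interval. Fix the model before the data are seen. Surgeon should be random and not a set of fixed effects, because fixed effects lose power when surgeons differ little.

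Optionally, include hospital and approach as terms in the TUG comparison. No change is asked for complications or mid-thigh pain on grounds of precision.

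The cost is slightly more analysis work and the need to record surgeon and approach for each operation, which the article does not say is already done. Surgical practice, allocation and sample size stay as they are.

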### Study variables

Preoperatively, social demographic data, the ASA classification, Groningen Activity Restriction Scale (GARS, from which the Parker mobility score can be derived) and the SF-12 are obtained from each patient. [10,12,13]

The main outcome measures of this study are the functional results, complication rate and duration of surgery of the hemiarthroplasty.

### Primary outcome measures

• Duration of surgery is defined as skin-to-skin surgical time, measured in minutes.

• Complications, divided in major and minor complications, are recorded during the follow up period of 1 year. The complications are ranked in the modified Elixhauser mode, as described by Parvizi.[11]

• Functional outcome is measured by the Timed-Up-and-Go (TUG) score and the Groningen Activity Restriction Scale (GARS). [10,14]

• Postoperative mid-thigh pain is defined as pain explicit in the front and mid part of the femur, and scored on a 4-point ordinal scale (non/mild/moderate/severe).

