#### Secondary outcome measures

We will use the chi-squared test or Fisher's exact test for the binary variables. In cases of paired binary data (outcome variables) we will use the McNemar test and a paired t-test for mean differences. In the case of a statistically significant association (*p *< 0.05), we will use a logistic regression to model the probability/odds of an outcome.

The variables obtained from the clinical evaluation will be tabulated and analysed as mean, standard deviation, minimum and maximum values. All analyses will be performed using SPSS software (SPSS Inc., Chicago, IL, USA).

Kaplan Meijer survival analysis will be done after final follow up, using failure (reoperation) and mortality as endpoints.

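### Mid-thigh pain (4-point ordinal) and complications are assigned a Student's t-test, although pain was sized as a comparison of two proportions and no rule turns the score into pain yes/no

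*Protocol article*

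**What the plan says.** - **Pain scale.** In the list of primary outcome measures (Methods and design), mid-thigh pain is "scored on a 4-point ordinal scale (non/mild/moderate/severe").
- **Complications.** The same list states: "Complications, divided in major and minor complications, are recorded during the follow up period of 1 year". It adds that they are ranked by a modified Elixhauser scheme.
- **Sizing of pain.** Determination of sample size, (b) Functional outcome, works with percentages of patients: "π1 = 30%, π 2 = 7.5%, π = (30%+7.5%)/2 = 18.75"%. The formula ends in "0,1875*(1-0,1875))/(0,225)^2 ^= 63.2" per group, and an increase of 35% for death and loss brings it to 86. This is the largest requirement stated; surgery time needs 46 and TUG 34 per group. The total is then set at 100 per group.
- **Primary test.** Statistical analysis, Primary outcome measures: "The differences in operation time, mid-thigh pain, complications and TUG test will be analyzed using a Student's t-test", at p < 0.05.
- **Tests for binary data.** Only under Statistical analysis, Secondary outcome measures: "We will use the chi-squared test or Fisher's exact test for the binary variables".

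**The concern.** One test is named for four primary outcomes. It suits operation time. For pain it does not match the scale or the sizing. A t-test on the score compares mean category codes (for example none = 0 to severe = 3), so it treats each step between categories as equal. Its result cannot be read against the 22.5-point difference in the percentage with pain, and the power behind the figure of 86 per group belongs to another analysis. The article does not say at which level of the score a patient counts as having pain.

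For complications, the article does not say what number per patient would be averaged: a count, a rank, or a yes/no indicator.

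This is more than a detail left to a later plan, because the article names the test. If it is left alone, the coding of a primary outcome may be chosen after the data have been seen.

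**Working it through.** **1. Reproducing the plan's figure.** Inputs from section (b): 30% and 7.5%, mean 18.75%, difference 0.225, multiplier 21.

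n = 21 × 0.1875 × 0.8125 / 0.225² = 63.19, which matches 63.2.

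63.19 × 1.35 = 85.3, rounded up to 86. This also matches.

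**2. What the multiplier implies.** 2 × (1.960 + 1.282)² = 21.0, that is two-sided 5% and 90% power; 80% power would give 15.7. The article does not state the power. The formula is the usual one for two proportions.

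**3. Power of the matching test.** A standard two-proportion calculation (normal approximation) gives 91% at 64 evaluable per group. It gives 92% at 65, which is what 100 per group leaves after a 35% loss (100 × 0.65).

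**4. Power of the test as written.** Simulation with 20,000 runs per row, 64 per group, pain in 30% versus 7.5%, and scores coded 0–3. The article gives no severity mix, so the mild/moderate/severe splits among patients with pain are assumptions. Any score above none is counted as pain, which is also an assumption.

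| Split in the 30% arm | Split in the 7.5% arm | Mean scores | Difference in means | t-test on 0–3 | Chi-squared, any pain |
|---|---|---|---|---|---|
| 60/30/10 | 60/30/10 | 0.450 vs 0.1125 | 0.3375 | 87% | 92–93% |
| equal thirds | equal thirds | 0.600 vs 0.150 | 0.450 | 88% | 93% |
| 80/15/5 | 50/30/20 | 0.375 vs 0.1275 | 0.2475 | 69% | 93% |
| 80/15/5 | 20/30/50 | 0.375 vs 0.1725 | 0.2025 | 45% | 92–93% |
| all mild | all severe | 0.300 vs 0.225 | 0.075 | about 16% | 92% |

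Each mean is the pain rate times the mean severity code. In the first row the mean code is 0.6×1 + 0.3×2 + 0.1×3 = 1.5, so the means are 0.30 × 1.5 = 0.45 and 0.075 × 1.5 = 0.1125. The 22.5-point difference is the same in every row, yet the quantity that the t-test examines runs from 0.075 to 0.45.

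Two other splits shared by both arms (80/15/5 and 50/30/20) give 86–88%. If all pain in both arms is mild, the score is a 0/1 variable and the two tests agree at about 93%.

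**5. Type I error.** With the same distribution in both arms, the t-test on the score rejects in about 4–5% of runs.

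**6. Complications.** No arithmetic applies. Section (c) gives no sample size for them, so the mismatch between test and sizing concerns pain only. What can be set side by side is an outcome made of major and minor events, called a rate under Study variables, and a test of means with no per-patient quantity defined.

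**The case against.** Much can be said for the plan. With similar severity in both arms, the t-test on the score loses only about 5 to 6 points of power. The low values in the table need severity to run against frequency, and nothing in the article suggests that it will. A t-test on a 0/1 pain indicator performs like chi-squared, and the article does not say which coding enters the test. The Elixhauser ranking may be what is meant to be averaged for complications. A fuller analysis plan may exist.

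These points limit the size of the problem. They also rule out three readings that a reader might infer:

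- **That the analysis cannot test the planned difference.** This is too strong, because a dichotomised score under a t-test would do so. What stands is that no dichotomisation is stated.
- **That the skew of the score makes the t-test invalid.** The type I error at these group sizes does not support this.
- **That the sample size for pain is wrong because of this.** The two-proportion arithmetic reproduces, and with a matching test 65 evaluable per group is enough for the implied power.

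Any pain versus none is a plausible reading of the percentages in section (b), but it is not stated there.

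The objection does not remove the mismatch itself. The named test, the outcome scale and the sizing refer to different quantities, and the tests that fit are named only for secondary outcomes.

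**Conclusion.** The point stands at moderate size. As written, the primary test for mid-thigh pain compares mean category codes, while the trial was sized on a difference in proportions. Under assumed severity mixes alike in both arms, the cost is a fall from about 93% to about 87–88% power at 64 per group. If the arm with less pain has the more severe pain, power falls further, to 69%, 45% or about 16% in the mixes tried; these are illustrations and not predictions. False-positive risk is not raised. For complications, the fault is that the quantity to be compared is undefined and a test of means is a poor fit for major/minor events; no power figure is at issue. The t-test for operation time is not in question.

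**What to change.** In Statistical analysis, Primary outcome measures:

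1. Limit the Student's t-test to the continuous outcomes.
2. For mid-thigh pain, state the cut-point that section (b) assumed (for example any pain versus none) and one primary time point. Report the risk difference with a 95% confidence interval and a chi-squared or Fisher test. An ordinal analysis of the four levels can be added as optional support.
3. For complications, compare the proportions of patients with at least one major and with at least one minor complication, each as a risk difference with a 95% confidence interval and a chi-squared or Fisher test.

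**Cost.** No extra patients or data are needed, and the article already names the tests. It is slightly more than a change of wording: the cut-point and time point are design decisions to be fixed before analysis, and dichotomising sets severity aside in the primary test. The 91–92% power holds for the uncorrected chi-squared test. With a continuity correction, 90% power needs 70 evaluable per group against the 65 expected, so Fisher's test would give somewhat less.

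Section (b) also places pain under a non-inferiority design and gives no margin for it. That is a separate matter, which this change does not settle.
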